### Randomization

A computer algorithm [30] generated a permuted block randomization sequence that will allocate participants to either the acupuncture or sham control acupuncture group to ensure balanced group sizes and allocation concealment. We will use opaque, sealed envelopes in sequential order to contain allocation information.

### Blinding

As this is a single-blinded trial, patients will not know which treatment approach they will undergo. During the data collection and analysis stages, the clinical researcher, assessor, and statistician will not share study information with each other. Blinding will be assessed after the last treatment using a questionnaire that asks participants if they were in the real treatment group or the sham treatment group. The possible responses are “real treatment group,” “sham group,” or “do not know.”

### Intervention

All practitioners in this trial are licensed TCM acupuncture therapists with at least 5 years’ clinical experience, and they will be trained to master the study protocol. The acupuncturist will be asked to administer the sham intervention as they would administer standard manipulation, with the same enthusiasm. All participants will continue to receive standard rheumatological care.

### Acupuncture group

The acupuncture intervention program was designed by a senior acupuncturist. The acupoints will be *Shenshu* (BL23), *Ganshu* (BL18), *Yanglingquan* (GB34), *Jizhong* (DU6), *Jinsuo* (DU8), *Mingmen* (DU4), and *Yaoyangguan* (DU3). We will use sterile, disposable stainless-steel needles 0.3 mm in diameter, and 25 or 40 mm in length, depending on the acupoints. After eliciting the Deqi response, the researcher will apply electro-acupuncture by connecting an acupoint nerve stimulator (HANS-200A) to *Shenshu* (BL23) and *Ganshu* (BL18) at a frequency of 2 Hz for 30 min. Electro-acupuncture intensity will be set according to the maximum intensity tolerated by each subject (0.9–3.0 mA). Other needles will be stimulated manually every 10 min. All needles will be left in place for 30 min.

### Sham control acupuncture group

The acupuncture points will be lateral to those in the *verum* acupuncture group. However, instead of using a 0.25-mm diameter, 25-mm long, sterile disposable stainless-steel needles inserted into acupoints 2–3-mm deep without manipulation and into non-acupoints, we will include NP1 (1 cm outward horizontally of *Shenshu* [BL23]), NP2 (*Ganshu* [BL18] level outward by 1 cm), NP3 (1 cm behind *Yanglingquan* [GB34]), NP4 (1 cm to the right horizontally of *Jizhong* [DU6]), NP5 (1 cm to the right horizontally of *Jinsuo* [DU8]), NP6 (1 cm outward horizontally of *Mingmen* [DU4]), and NP7 (1 cm outward horizontally of *Yaoyangguan* [DU3]). Next, electro-acupuncture will be applied to *Shenshu* (BL23) and *Ganshu* (BL18; 0.1–0.3 mA). All needles will be left in place for 30 min. The inclusion of a placebo group will allow for comparison of active acupuncture care effects with manifestations of either sham treatment or psychic solace.

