## Discussion

The purpose of this trial is to assess the impact of acupuncture in the management of AS. It is clear that increased muscle stiffness is associated with poor range of motion [48], and a chronic inflammatory condition has significant impact on QoL. Patients report that back pain, arthralgia, and stiffness influence their daily work productivity and nocturnal sleep quality [49]. Acupuncture is used to reduce muscle stiffness and increase somatic activity in AS patients, and it is monitored by musculoskeletal-ultrasound techniques that, if less operator dependent, could obtain more-stable and reliable results [50]. The design of an appropriate control group for a clinical trial is critical. We will set a healthy-control group for baseline comparison, as there is currently no standardized for musculoskeletal-ultrasound measurement of AS. However, it is difficult to use placebo needles for controls. Therefore, we will use non-acupoints and superficial puncturing, which are considered ineffective, in the sham acupuncture group.

NSAIDs are often first-line treatment for AS, and biologics are the next step up. However, patients who have inadequate response to NSAIDs but cannot afford biologics often experience significant pain and impairment of their QoL [51]. This trial would provide evidence for acupuncture care for this group of patients.

Despite the measures taken to ensure a well-controlled trial, there are several methodological limitations to this study. The treatment intervention duration of 12 weeks might make it difficult to ensure patient compliance. Other aspects such as the trial results are meant to describe an approach to treatment for the typical patient and cannot anticipate all possibilities; clinicians must make careful clinical assessments based on sound clinical judgment of each patient’s circumstances and consideration of the patient’s preferences. In spite of its limitations, we hope that the trial will help provide new insights into the value of acupuncture and the evidence of musculoskeletal-ultrasound measures in AS.

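### The sham arm is described as non-acupoint needling, yet its weaker current is said to go to BL23 and BL18, the points electro-stimulated in the active arm; the sections must be reconciled

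*Protocol article*

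**What the plan says.** Three sections of the protocol article describe the two needling arms.

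- **Acupuncture group.** Seven acupoints are needled. The current is given by "connecting an acupoint nerve stimulator (HANS-200A) to *Shenshu* (BL23) and *Ganshu* (BL18) at a frequency of 2 Hz for 30 min". No other point in this arm receives current. On strength: "Electro-acupuncture intensity will be set according to the maximum intensity tolerated by each subject (0.9–3.0 mA").
- **Sham control acupuncture group.** The general rule is "The acupuncture points will be lateral to those in the *verum* acupuncture group". Seven sites follow, each defined by its offset from one active point. The first two are "NP1 (1 cm outward horizontally of *Shenshu* [BL23"]) and "NP2 (*Ganshu* [BL18] level outward by 1 cm"). No needle is listed at BL23 or BL18 themselves. The section then says "Next, electro-acupuncture will be applied to *Shenshu* (BL23) and *Ganshu* (BL18; 0.1–0.3 mA").
- **Discussion.** The rationale is that "we will use non-acupoints and superficial puncturing, which are considered ineffective, in the sham acupuncture group".

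The Study setting section adds that this arm is the placebo control against which clinical efficacy is judged.

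**The concern.** The efficacy claim is the difference between the acupuncture and sham arms. For that difference to mean acupuncture against an ineffective control, the text must say consistently where the sham is applied. Here it says two things. The list of sites and the Discussion describe non-acupoints. The sentence on current names two acupoints, the same two that carry current in the active arm.

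If the sentence on current is taken at its word, the control is not the one that the Study setting and Discussion sections describe. A null result would then be hard to read: acupuncture might have no effect, or the control might have been partly active. A positive result would describe a different contrast from the one claimed.

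**Working it through.** The article gives no figure that depends on the sham site, so there is none to reproduce. The check sets the statements side by side and compares the two current ranges.

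**1. Site of the current**

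| Item | Acupuncture group | Sham group |
|---|---|---|
| Needle sites listed | BL23, BL18 and five other acupoints | NP1 to NP7, all offset from the acupoints |
| Counterparts of BL23 and BL18 | the points themselves | NP1 and NP2, each 1 cm away |
| Points named for current | BL23, BL18 | BL23, BL18 |

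The points named for current coincide, 2 of 2. In the sham column the second and third rows disagree: the needles are at NP1 and NP2, but the current is said to go to BL23 and BL18.

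**2. Strength of the current**

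Inputs: active 0.9–3.0 mA (Acupuncture group section); sham 0.1–0.3 mA (Sham control acupuncture group section). The ratio is active divided by sham.

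- Smallest possible: 0.9 / 0.3 = 3
- Lower ends: 0.9 / 0.1 = 9
- Upper ends: 3.0 / 0.3 = 10
- Largest possible: 3.0 / 0.1 = 30

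The ranges do not overlap. The active section also asks for a Deqi response and for manual stimulation of the remaining needles every 10 minutes; the sham section asks for neither.

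**3. Needle site and depth in the sham arm**

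The sentence that should settle this does not. Its grammar presents shallow insertion of 2–3 mm, without manipulation, as the technique being replaced, and it mentions both acupoints and non-acupoints as places of insertion. The Discussion presents superficial puncture of non-acupoints as the technique being used.

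**4. What each reading implies**

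- *Current at BL23 and BL18, as written:* the electrical contrast is lower against higher current at the same acupoints, alongside the other needling differences. This disagrees with the rule that sham points lie beside the active ones and with the Discussion.
- *Current at NP1 and NP2, with BL23 and BL18 as shorthand:* this agrees with the list and the Discussion, but it is not what the sentence says.

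**5. Direction of any effect**

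If acupuncture is beneficial and the sham carries part of that benefit, the expected difference between arms is smaller than acupuncture against an inert control would give. The bias is toward zero. Its size depends on how active the sham is, and the article gives nothing from which to estimate that.

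**The case against.** **The currents differ greatly.** This stands. With a ratio of at least 3 and no overlap, a reader who infers from the shared points that sham patients receive the active treatment goes too far. The objection does not remove the contradiction. The Discussion calls non-acupoints and superficial puncture ineffective; it makes no such statement about low current at BL23 and BL18.

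**BL23 and BL18 may be shorthand for NP1 and NP2.** This is plausible, since those sites are defined only by reference to the acupoints. It rules out the inference that the sham cannot be carried out. It remains a guess: the section introduces the NP labels and then does not use them for the electrodes.

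**The article condenses a fuller protocol, and practitioners are trained on it.** This is fair. Nothing shows that any practitioner works from this sentence or that patients have received different shams, so inconsistent delivery is a possibility to check and not a finding. The point is still more than a detail left to the fuller document, because the article states the sites explicitly and the statements conflict.

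**The garbled needle sentence is a language fault.** Probably so, and the Discussion indicates the intent. It matters here only because it cannot be used to resolve the question of site.

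**Bias toward zero cannot create a false claim of superiority.** Correct. The risk is a masked effect and a mislabelled contrast.

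Two further inferences are unsupported. A reader might attach a loss of power to this point, but that needs an assumed share of effect in the sham arm for which the article gives no basis. A reader might also treat electro-stimulation as the main ingredient of the treatment; the protocol does not rank it above the other needling.

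**Conclusion.** The contradiction is real and lies in the current text. The sham section disagrees with itself, and with the Discussion, on where the sham current is applied, and its needle sentence is too garbled to decide the matter. As written, both points named for current are shared between arms, at sham currents 3 to 30 times lower than the active ones.

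The supported conclusion is that the comparator is not consistently described, and that on the literal reading it is not the non-acupoint placebo on which the efficacy claim rests. Whether the literal reading is what patients receive cannot be told from the article. The direction of any bias, toward zero, assumes that acupuncture helps and that sham activity works the same way; its size cannot be estimated. The documents do not support saying that the control is not a sham at all.

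**What to change.** Reconcile the Acupuncture group, Sham control acupuncture group and Discussion sections. State once, for the sham arm, the electrode sites, needle sites, insertion depth and needle type, and make every other mention agree. Which site, depth or current is right is for the investigators to say; this review takes no view.

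The Trial status section says that recruitment is under way, so confirm from the treatment records what sham patients have received so far and whether it was the same for all. Describe the comparison and word the conclusion as the contrast delivered. If any sham patients had current at BL23 or BL18, report that.

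The cost is a protocol clarification, a note to the acupuncturists and a check of treatment records. Clarifying the text needs no change to the sample size or the analysis.

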### Health control group

No acupuncture intervention will be conducted in healthy controls.

### Outcomes

#### Primary outcomes

Primary outcomes will be musculoskeletal-ultrasound, Ankylosing Spondylitis Quality of Life Scale (ASQoL) results, pain severity, and Bath Ankylosing Spondylitis Metrology Index (BASMI) results. Musculoskeletal ultrasound will use two-dimensional (2D) grayscale, shear-wave elastography (SWE) and superb microvascular imaging (SMI) techniques. The 2D grayscale technique will capture muscle thickness changes in the paraspinal and multifidus muscles. Changes in lumbar-muscle thickness can reflect muscle morphological change due to acupuncture treatment for somatic disorders. The lumbar paraspinal muscles play important roles in movement and control of the spine; studies have shown an inverse relationship between lumbar paraspinal-muscle CSA and lower-back disability but not between lumbar paraspinal-muscle CSA and pain intensity, suggesting that treatment strategies directed at increasing paraspinal-muscle size might be effective in reducing lower-back disability [31]. Later, a blinded tester will measure thickness at the levels of the L4–5 zygapophyseal joints using onscreen calipers [32]. SWE is an ultrasound technique that characterizes tissue mechanical properties based on the propagation of remotely induced shear waves [33]. It provides semiquantitative (color map) and quantitative (absolute SWE value) imaging biomarkers that are useful in assessing the elasticity of tendon and muscle composition and stiffness [34, 35] and in helping to distinguish between asymptomatic and symptomatic [36], with diseased tendons being significantly softer than healthy ones [37]. SMI is an ultrasound technique for vascular and microvascular examination. It can diagnose diseases associated with angiogenesis in their early phases and has value in grading disease activities and monitoring therapeutic responses [38]. SMI uses an intelligent algorithm that efficiently separates low-speed flow signals from motion artifacts and successfully extracts clinically relevant information [39]. We will test AS participants using SMI, record resistance index (RI), peak systolic velocity (PSV), and end diastolic velocity (EDV) to reflect SIJ inflammation in this trial. Ultrasound tests will be performed at baseline and week 12.

The ASQoL, Pain-Visual Analogue Scale for pain (VAS), and BASMI scales have anchors of 0 (none) to 10 (severe). Participants will evaluate their conditions over the preceding week. ASQoL records the impact of AS on health-related QoL from the patient’s perspective in terms of sleep, mood, motivation, coping, activities of daily living, independence, relationships, and social life [40]. It is a fixed-response questionnaire that asks endorsement (yes/no) of 18 items, and the total score is the sum of each score. Higher scores reflect low QoL. Regarding reliability, Cronbach’s α is reported between 0.89 and 0.92 in the different study groups. Regarding validity, ASQOL correlates moderately well with other AS-specific health outcome measures.

The Pain-VAS is selected to quantitatively evaluate the overall pain level of the body. BASMI [41] is associated with QoL, physical function, and psychological status and reflect the change of lumbar side flexion sensitive and reproducible. It is a composite score based on 5 direct measurements of spinal mobility [42]: lateral lumbar flexion, tragus-to-wall distance, lumbar flexion, intermalleolar distance, and cervical rotation angle, take the mean of the left and right measurements. Add together the scores for each item. Divide this by 5 to give the final BASMI score. The higher the BASMI score, the more severe the patient’s limitation of movement due to their AS. BASMI reliability has been shown to be good. Regarding construct validity, the BASMI has been shown to discriminate between patients with and without radiographic change due to AS.

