**Methods:**

We will recruit a total of 60 participants diagnosed with AS and 30 healthy subjects. Participants will be randomly allocated 1:1 to either an acupuncture group or a sham control acupuncture group. Primary-outcome measures will be musculoskeletal ultrasound, Ankylosing Spondylitis Quality of Life Scale (ASQoL), Bath Ankylosing Spondylitis Metrology Index (BASMI), and the Visual Analogue Scale (VAS) for pain. Secondary outcome measures will be the Bath Ankylosing Spondylitis Disease Activity Index (BASDAI), Bath Ankylosing Spondylitis Function Index (BASFI), and Fatigue Scale-14 (FS-14). We will monitor the effect of acupuncture or sham acupuncture on blood flow and SIJ inflammation using SMI, lumbar-muscle stiffness using SWE and the lumbar paraspinal-muscle cross-sectional area (CSA) using a two-dimensional (2D) grayscale imaging. QoL, physical function, and fatigue will be assessed using an evaluation scale or questionnaire developed for this study, with outcomes measured by the ASQoL, BASMI, BASDAI, BASFI, and FS-14. Healthy subjects will not receive acupuncture but undergo only musculoskeletal ultrasound at baseline. Acupuncture and sham control acupuncture interventions will be conducted for 30 min, 2–3 times/week for 12 weeks. Musculoskeletal ultrasound will be conducted at baseline and post-intervention, while other outcomes will be measured at baseline, 6 weeks, and post-intervention. The statistician, outcome assessor, and participants will be blinded to treatment allocation.

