### Data analysis

We will use SPSS software version 18.0 (IBM Corp, Armonk, New York, US) to perform data analysis. Demographic and baseline data will be analyzed with standard descriptive statistics. Data will be presented as the mean ± standard deviation (SD). Between-group differences will be tested using repeated-measure analyses of variance (ANOVAs). The entire data analysis process will be performed by statisticians who are independent from the research team and blinded to the group settings. The accepted level of significance for all analyses will be *P* < 0.05.

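### Four equal-rank primary outcomes, about eight variables once ultrasound is unpacked, share a 0.05 threshold with no stated adjustment, ranking or success rule

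*Protocol article*

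**What the plan says.** The Primary outcomes section of the protocol article lists four outcomes side by side: "Primary outcomes will be musculoskeletal-ultrasound, Ankylosing Spondylitis Quality of Life Scale (ASQoL) results, pain severity, and Bath Ankylosing Spondylitis Metrology Index (BASMI) results". The abstract and the Fig. 2 legend give the same four, and none is ranked above the others.

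Ultrasound is described as a set of techniques: "Musculoskeletal ultrasound will use two-dimensional (2D) grayscale, shear-wave elastography (SWE) and superb microvascular imaging (SMI) techniques". For SMI, the investigators will "record resistance index (RI), peak systolic velocity (PSV), and end diastolic velocity (EDV) to reflect SIJ inflammation in this trial". For grayscale, the Primary outcomes section says: "The 2D grayscale technique will capture muscle thickness changes in the paraspinal and multifidus muscles". The abstract instead describes the ultrasound readings as "lumbar-muscle stiffness using SWE and the lumbar paraspinal-muscle cross-sectional area (CSA) using a two-dimensional (2D) grayscale imaging". No single reading is named as the primary ultrasound result.

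The Data analysis section gives one threshold: "The accepted level of significance for all analyses will be *P* < 0.05". Between-group differences are to be tested by repeated-measures ANOVA. The Study setting section calls this a superiority trial, and the Sample size section rests on pain VAS alone, at an alpha of 0.05.

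**The concern.** Several primary outcomes, each judged at 0.05, give several chances to claim superiority. The article does not say whether one significant primary result is enough, whether all four are needed, or whether they are tested in an order. The reading that any one suffices therefore stays open, and under it the chance of a false claim across the set exceeds 5%.

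The ultrasound outcome makes this worse because it is a family of readings. Unless one is chosen beforehand, whichever reading gives the smallest P value could be presented as the primary ultrasound result. The difference between thickness and cross-sectional area adds a second open choice, since these are different quantities.

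This is more than detail left for an analysis plan. The article itself makes four outcomes primary, fixes one threshold for all analyses, and describes the same grayscale outcome in two ways.

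**Working it through.** **The plan's own figure.** The article states no family-wise error rate, so there is none to reproduce. The nearest figure is the per-analysis level of 0.05.

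**Counting the primary variables.**

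| Named outcome | Variables | Count |
|---|---|---|
| ASQoL | total score | 1 |
| Pain | VAS | 1 |
| BASMI | composite score | 1 |
| Ultrasound, grayscale | muscle thickness (Methods) or cross-sectional area (abstract) | 1 |
| Ultrasound, SWE | muscle stiffness | 1 |
| Ultrasound, SMI | RI, PSV, EDV | 3 |

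That makes 4 named outcomes and 3 + 5 = 8 variables. Thickness and cross-sectional area are counted once, as two descriptions of one grayscale outcome.

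**Independent tests.** With k tests at two-sided 0.05 and no true effect on any of them, P(at least one significant) = 1 − 0.95^k:

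- k = 4: 1 − 0.8145 = 18.5%
- k = 8: 1 − 0.6634 = 33.7%

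**Correlated tests.** The documents give no correlations between outcomes, so a range was assumed. Test statistics were simulated as Z_j = √ρ·U + √(1 − ρ)·E_j, with U and E_j independent standard normal and 1,000,000 draws. A two-sided false positive is |Z_j| > 1.96 for at least one j. A false positive favouring acupuncture is Z_j > 1.96 for at least one j, with every outcome scored so that higher is better. For independent tests the latter is 1 − 0.975^k.

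| Assumed ρ | Either direction, k = 4 | Either direction, k = 8 | Favouring acupuncture, k = 4 | Favouring acupuncture, k = 8 |
|---|---|---|---|---|
| 0 | 18.5% | 33.7% | 9.6% | 18.3% |
| 0.5 | 15.6% | 25.1% | 7.8% | 12.5% |
| 0.8 | 11.4% | 15.8% | 5.7% | 7.9% |

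The benchmarks are 5% in either direction and 2.5% in favour of acupuncture. Every cell is more than twice its benchmark.

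**Effect of an adjustment.** Bonferroni across four outcomes uses 0.05/4 = 0.0125, and 1 − (1 − 0.0125)^4 = 4.9% for independent tests. Holm starts at the same 0.0125 for the smallest P value and relaxes to 0.05/3 = 0.0167, then 0.025, then 0.05. It holds the family-wise rate at or below 5% whatever the correlation.

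**The case against.** The strongest reply is that the success rule is inferred. No section says that one significant primary makes the trial positive. If all four had to succeed, the chance of a false overall claim would be at most 5%. The full protocol and any analysis plan are not shown, and a multiplicity procedure is often placed there. Adjusted P values can also be compared with 0.05, so the sentence in Data analysis does not exclude Holm. All of this stands, which is why the percentages are conditional on the any-one-suffices reading. It does not remove the point. The article fixes four equal primaries and one threshold without saying how they combine, and an all-must-succeed rule would need joint power that a sample size built on pain VAS alone does not address.

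Four stronger readings are tempting, and the documents do not support them.

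- **Nine tests and a 37% error rate.** A reader might add cross-sectional area to thickness and compute 1 − 0.95^9 = 37.0%. The two are conflicting descriptions of one grayscale outcome, so counting both contradicts calling them a conflict. Independence is also least plausible for RI, PSV and EDV, which are flow readings from the same joint.
- **A false claim for acupuncture at the two-sided rate.** The two-sided rates include false results favouring sham. Those favouring acupuncture are about half.
- **Repeated visits add further error.** The Data analysis section specifies repeated-measures ANOVA, and no section plans a separate test at each visit. Ultrasound is fixed at baseline and week 12. The week-24 VAS in the Sample size section comes from the cited study, and the schedule figures are not shown, so an unfixed primary time cannot be established from the abstract.
- **No error control at all.** Each test is held at 5%. What is unstated is control across the set.

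**Conclusion.** The point holds in this form: four equal-rank primary outcomes, one of them a family of at least five ultrasound readings, are judged at 0.05 with no stated hierarchy, success rule or adjustment, and the grayscale reading is defined in two ways. On the reading that any one significant primary suffices, the two-sided chance of at least one false positive runs from about 11% (four tests, ρ = 0.8) to 34% (eight independent tests). In favour of acupuncture it is roughly 6–18%.

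These figures assume no true effect on any primary variable, a success rule that the article leaves open, and equal pairwise correlations that are not in the documents. The absence of a rule for combining the primaries, the unchosen ultrasound variable and the conflict between thickness and cross-sectional area do not depend on those assumptions.

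**What to change.** Before unblinding:

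1. Name one primary ultrasound measure and make the remaining ultrasound readings secondary.
2. Use the same grayscale measure, thickness or cross-sectional area, in the abstract and the Methods.
3. State that the four primary outcomes are tested with Holm at a family-wise two-sided 0.05.

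The investigators may instead choose a single primary outcome or a fixed testing order; either also controls the error. Making pain VAS the sole primary is not the obvious choice. It would demote the ultrasound question in the trial's title and first hypothesis, and its sample-size basis is a week-24 score from another study.

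The cost is wording in the protocol and analysis plan and a registry update, with no change to data collection. Each primary outcome faces a stricter threshold, and the power statement should say so. The stated 23 per group matches a standardised difference of 1 (n = 22.02, rounded up). At that difference, the first Holm step of 0.0125 lowers two-sided t-test power from 91% to 78% with 23 per group, and from 97% to 90% with 30.

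The difference and SD actually stated give 0.36/0.72 = 0.5, which needs about 86 per group at 0.05 and about 116 at 0.0125. With 30 per group, power is already only 48% at 0.05. That mismatch is a separate problem in the Sample size section, but it must be settled before power under any adjusted threshold can be stated.
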